#### Exclusion criteria

Patients must not fulfil any of the following criteria:
GastrectomyIntestinal resection;Other known organic gastrointestinal diseases (e.g. inflammatory bowel disease (Crohn’s disease, ulcerative colitis));Unable or unwilling to stop restricted medication including regular loperamide, antispasmodics (e.g. buscopan, mebeverine, peppermint oil, alverine citrate), eluxadoline, tricyclic antidepressant doses > 30 mg/day or other drugs likely in the opinion of the investigator to alter bowel habit. These medicines should be discontinued for a 7-day washout period prior to registration;QTc interval ≥ 450 msec in men or ≥ 470 msec in women (assessed within the last 3 months by electrocardiogram (ECG));Previous use of ondansetron for chronic symptoms, or contraindications to ondansetron;Pulse, blood pressure, laboratory-tested blood values outside the normal ranges according to the site’s local definition of normal (assessed within the last 3 months). Note minor rises in alanine aminotransferase (ALT) (< 2 × upper limit of normal) will be acceptable, but the patient’s General Practitioner (GP) will be informed if ALT remains elevated at the end of the trial;Women who are pregnant or breastfeeding;Patients currently or previously participating in a trial of an investigational medicinal product (IMP) in the previous 3 months, where the use of the IMP may cause issues with the assessment of causality in this trial;Patients who have started or who have had alterations to their dosage of selective serotonin re-uptake inhibitors or tricyclic antidepressants in the last 3 months, or who will have their dosage changed during the trial;Patients currently taking and unwilling or unable to stop taking apomorphine or tramadol (which interact with ondansetron);Patients with only stools of consistency 7 on the BSFS for 7 days a week.

Patients taking QT-prolonging or cardiotoxic drugs will be reviewed by the local Principal Investigator (PI) to determine whether they are suitable for the trial.

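### The 7-day washout offered to patients on tricyclics above 30 mg/day cannot work alongside the 3-month dose-stability exclusion in the same list

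*Protocol article*

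**What the plan says.** The Exclusion criteria section of the protocol article opens with "Patients must not fulfil any of the following criteria", so each item excludes on its own.

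The restricted-medication item covers patients who are "Unable or unwilling to stop restricted medication including regular loperamide". Its list also takes in antispasmodics, eluxadoline and "tricyclic antidepressant doses > 30 mg/day or other drugs likely in the opinion of the investigator to alter bowel habit". It ends with the washout: "These medicines should be discontinued for a 7-day washout period prior to registration".

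A later item in the same list deals with antidepressant stability. It excludes patients who recently started such a drug and those who "had alterations to their dosage of selective serotonin re-uptake inhibitors or tricyclic antidepressants in the last 3 months". The same item also looks ahead, with a further limb for planned changes: "or who will have their dosage changed during the trial".

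The Visit 1 text under Participant timeline repeats the first item in short form: medication is reviewed, and a patient who cannot come off drugs that affect bowel habit may not enter. It makes no special provision for tricyclics and does not mention the 3-month item.

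**The concern.** The first item reads as a route into the trial: a patient above the tricyclic threshold who is able and willing to stop, and who completes a week off the drug, is not excluded by it. The second item appears to close that route, because the step taken to meet the first is itself a recent change in tricyclic dosage.

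Three things are at stake:

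- **Consistency across sites.** The trial starts at 18 sites and may use up to 24, and each applies this list. Sites may decide the same patient differently.
- **The patient.** Someone may stop an antidepressant in order to qualify and become ineligible because of it.
- **The per-protocol set.** The Endpoint analysis section gives patients randomised and later found ineligible as its example of those left out of the per-protocol analysis of the primary endpoint. Whether a recent tricyclic stopper or reducer belongs in that group depends on which item is taken to govern.

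**Working it through.** The plan states no figure to reproduce. The check sets the two items side by side and then compares dates.

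**Step 1: what each item does to a patient above the threshold**

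| Patient's position | Restricted-medication item | 3-month item |
|---|---|---|
| Cannot or will not stop | Excluded | Not reached |
| Recently reduced to 30 mg/day or less | Not excluded, since only "tricyclic antidepressant doses > 30 mg/day" are restricted | Excluded: plainly a change of dosage |
| Recently stopped, 7 days off drug | Not excluded | Excluded, if stopping counts as an alteration |
| Stopped or reduced more than 3 months ago | Not excluded | Not excluded |

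The conflict lies in the second and third rows. For those patients the first item asks for a change and the second penalises it.

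**Step 2: does the reference date matter?**

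The article does not say from which date the 3 months are counted, so every candidate date is tried.

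Inputs:
- Washout: 7 days before registration at visit 1 (Exclusion criteria).
- Visit 1 to visit 2: 2 weeks, or 14 days (Visit 2).
- Visit 2 to visit 3: at least 6 days for transit-study patients, who take marker capsules over that period (Visit 2).
- Look-back window: 3 months, taken as about 90 days (assumption).

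Time since a change made with the shortest permitted washout:
- At registration: 7 days, which is 90 − 7 = 83 days short of the window.
- At visit 2, where eligibility is confirmed: 7 + 14 = 21 days, which is 90 − 21 = 69 days short.
- At visit 3, where patients are randomised: 7 + 14 + 6 = 27 days, which is 90 − 27 = 63 days short.

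The change falls inside the look-back on all three dates, so the choice of reference date does not rescue the 7-day route. The 27 days is a minimum, but the visit 2 to visit 3 gap would have to be about 63 days longer before the visit 3 reading came out differently.

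**Step 3: is there a linking exemption?**

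Neither item refers to the other, and the Visit 1 text adds nothing on tricyclics. The conflict is confined to tricyclics: the other named restricted medicines are not under the 3-month item, so for them the 7-day washout works as written.

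**The case against.** **The list is cumulative, so there is no contradiction.** A reader might infer that the two items give flatly opposite answers. They do not. The first item never declares anyone eligible; it only declines to exclude. Read literally, the list gives one answer for a recent change (excluded), and a patient whose change is more than 3 months old meets both items. This stands. What remains is that the 7-day washout then serves no purpose for tricyclics, although the item names them as one of the drugs it covers.

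**The items address different patients.** One speaks of stopping; the other speaks of starting or altering a dosage, which could be meant for those who stay on an antidepressant. On that reading a full stopper escapes the 3-month item. This is a fair reading, but the text does not state it. Nor does it help a patient who cuts down to the permitted range.

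**The statistical harm is not shown.** A reader might infer that a baseline diary begun a week after withdrawal is unsettled, that later drift counts as response in both arms, and that the treatment contrast is diluted. The documents give no direction, size or duration for any withdrawal effect, and no rationale for the 3-month item. Such patients could fall in either arm, allocation is minimised by site, and the main analysis is by intention to treat. That inference is not supported.

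**Divergence between sites is not demonstrated.** This is correct. The wording allows it, and no more than that can be said.

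**Conclusion.** The point holds as a drafting conflict between two eligibility items. As written, the 7-day washout cannot make a recent tricyclic reducer eligible, and arguably cannot make a recent stopper eligible either. For the reducer this rests on the text alone, with 3 months taken as about 90 days. For the stopper it also requires that discontinuation count as an alteration of dosage, which the article leaves open.

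The number of patients affected cannot be derived. The documents do not say how many candidates take tricyclics above the threshold, and an assumed share of the 400 to be randomised would not measure it: on the literal reading none of the affected patients should be randomised at all. Not every such candidate is affected either, since those who will not stop are excluded anyway and those who changed more than 3 months ago pass both items.

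The consequences that stand are who may be enrolled, the risk of a patient stopping a medicine to no purpose, and an unclear boundary for the per-protocol set. The sample size is untouched, and neither bias between arms nor an effect on the primary test is shown. The matter is modest in scale but wrong as written.

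**What to change.** Reconcile the two items so that each patient taking a tricyclic gets one eligibility answer, the same at every site. This can be done by removing tricyclics from the medicines to which the 7-day washout applies, or by stating whether a change made to meet the restricted-medication item is exempt from the 3-month item. The choice is a clinical one for the sponsor and clinical leads, and this review does not favour either window. The reconciled wording should make clear whether full discontinuation counts as an alteration, and the same answer should be used when deciding who is ineligible for the per-protocol analysis.

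The cost is about one sentence in the eligibility criteria and a note to sites. Depending on the choice made, some candidates may enter later or not at all.

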### Intervention

Eligible patients will be randomised in equal proportions to receive either over-coated capsules of ondansetron 4 mg or over-coated placebo, for 12 weeks. The dose of the IMP will be individually titrated during the first 2 weeks by calls from the research team on alternate days, aiming for a stool consistency type 3–5 on the BSFS.

#### Adherence

Patients will receive face-to-face adherence reminders on each trial visit, as well as the phone calls during the 2-week titration period. Any remaining IMP capsules are counted at visits 4 and 5.

#### Dose titration

Since the optimum dose varies widely from 4 mg on alternate days up to 8 mg t.d.s., we will start all patients on 4 mg daily and after 2 days contact them to adjust the dose, thus avoiding the complication of constipation. If stool consistency remains loose, patients will be asked to increase their dose in 4-mg steps every 2 days up to the maximum of 8 mg t.d.s. If stools become hard or there is no bowel movement on day 2, they will be asked to stop the drug for 1 day and recommence at a lower dose changing from 4 mg daily to 4 mg on alternate days. If stools still remain hard or infrequent, patients will be asked to reduce their dosage to 4 mg every third day. Patients will discontinue the trial in the unlikely event that their stool remains hard even at this low dose.

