### Trial design

TRITON is a multi-site, parallel group, randomised, double-blind, placebo-controlled trial with embedded mechanistic studies within selected sites. Our aim is to determine the superiority of ondansetron compared with placebo. In total, 400 patients with IBS-D will be randomised 1:1 to receive either ondansetron or placebo. Both treatments will be administered in oral doses of between 4 mg every third day and 24 mg daily for 12 weeks. Dose titration will be undertaken in the first 2 weeks of the trial to avoid constipation, which at a standard dose occurs in one quarter of patients. The primary outcome will be assessed over the 12 weeks post randomisation. Secondary and safety outcomes will be measured up to 16 weeks following randomisation. See Fig. 1 for an overview of the trial procedures. The Standard Protocol Items: Recommendations for Interventional Trials (SPIRIT) checklist is provided as an Additional file 1.

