#### Endpoint analysis

All analyses will be conducted on the intention-to-treat population, defined as all patients randomised regardless of non-compliance with the intervention. The primary endpoint will be analysed per-protocol to indicate whether results are sensitive to the exclusion of patients who violated the protocol (e.g. those patients randomised but subsequently found to be ineligible). Primary and secondary analysis will be performed blinded to random allocation. Outcome measures will be analysed by regression models appropriate to the data type. Such analyses will be adjusted for randomisation minimisation factors: site, completion of manometry assessment, barostat assessment, and baseline values where applicable, age, and gender. Baseline characteristics will be summarised by randomised group.

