#### Primary analysis

The primary analysis will compare the difference between treatment groups in the proportion of patients achieving the FDA-recommended endpoint at 12 weeks post-randomisation, using a logistic regression model adjusted for minimisation, age, and gender. Any missing data will be assumed missing at random (MAR) and imputed for the primary analysis. Odds ratios and corresponding 95% confidence intervals will be presented.

Sensitivity will be analysed to assess the impact of missing data on the treatment effect. This will include complete case analysis and alternatives to multiple imputation (e.g. pattern mixture modelling) if missing patterns suggest data are missing not at random.

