#### Safety analyses

All patients who receive at least one dose of trial treatment will be included in the safety analysis set. The number of patients reporting a SAE (up to 28 days after the last dose of treatment) and details of all SAEs will be reported for each treatment group. The number of patients withdrawing from trial treatment will be summarised by treatment arm, along with reasons for withdrawal. All safety analyses performed prior to final analysis will be undertaken by the safety statistician (rather than the trial statistician), thus ensuring that the trial team remain blinded.

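### Read literally, the hard-stool exit rule ends follow-up as well as treatment, which sits badly with the intention-to-treat analysis; the likely effect is small and its direction uncertain

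*Protocol article*

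**What the plan says.** The last sentence of Dose titration deals with patients whose stool is still hard at the lowest step: "Patients will discontinue the trial in the unlikely event that their stool remains hard even at this low dose". The object of that sentence is the trial, not the treatment.

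Three other statements bear on it:

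- **Endpoint analysis** uses the "intention-to-treat population, defined as all patients randomised regardless of non-compliance with the intervention".
- **Safety analyses** has the narrower term: "The number of patients withdrawing from trial treatment will be summarised by treatment arm, along with reasons for withdrawal".
- **Primary analysis** handles gaps as follows: "Any missing data will be assumed missing at random (MAR) and imputed for the primary analysis". Its sensitivity analyses are a complete-case analysis and "alternatives to multiple imputation (e.g. pattern mixture modelling) if missing patterns suggest data are missing not at random".

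On timing, Trial design says: "Dose titration will be undertaken in the first 2 weeks of the trial to avoid constipation". The Visit 3 section allows later dose changes to avoid constipation, so a later exit is possible, but most would be expected early. Nothing in the article says that diary, text messages or visits continue after this exit, and nothing says outright that they stop.

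**The concern.** An intention-to-treat analysis of all randomised patients works best when outcomes are still collected from those who stop treatment. A rule that removes patients from the trial because of how their bowel responded creates missing data for a reason related to treatment effect. Missing at random is least comfortable in that situation. The last diary days before exit would show hard stools, so the loose-stool half of the endpoint would look met just before the patient stops the capsules. What happens to stool and pain afterwards would not be seen.

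Safety data are exposed too. The Adverse events section records reportable events at visits 4, 5 and 6, and visit 4 falls at 6 weeks. The titration calls check for serious events only. A patient who leaves in week 1 or 2 would never complete the checklist, although safety is part of the primary objective and constipation is the harm that titration is meant to avoid.

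**Working it through.** **1. The plan's own figure.** Inputs from Sample size: placebo 17%, difference 15 points (so ondansetron 32%), 90% power, two-sided 5%, 15% attrition. With the pooled-variance formula for two proportions and mean rate 0.245:

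n per arm = [1.960 × √(2 × 0.245 × 0.755) + 1.282 × √(0.17 × 0.83 + 0.32 × 0.68)]² / 0.15² ≈ 171, so 342 in total. Then 342 / 0.85 gives 403. The unpooled version gives 168 per arm, 336 in total and 396 after attrition. The stated 400 is reproduced, and this point does not affect it.

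**2. How much of the endpoint would be unobserved.** Response needs at least 6 qualifying weeks of 12. An exit at the end of week 2 leaves 12 − 2 = 10 weeks unseen. Two observed weeks cannot establish response, which needs 6. Nor can they rule it out, which needs 7 non-qualifying weeks. Responder status would therefore depend on imputed weeks.

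**3. Effect on the treatment difference.** Assumptions: a share f of the 200 ondansetron patients exits, no placebo patient exits, those who stay respond at 32% and placebo patients at 17%. Imputing exits at the arm rate leaves the difference at 32 − 17 = 15.0 points for any f. The extremes for the true difference are:

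- all exits are non-responders: 32 × (1 − f) − 17
- all exits are responders: 32 × (1 − f) + 100 × f − 17

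| f | Exits of 200 | All non-responders | All responders |
|---|---|---|---|
| 1% | 2 | 14.7 | 15.7 |
| 2% | 4 | 14.4 | 16.4 |
| 5% | 10 | 13.4 | 18.4 |
| 10% | 20 | 11.8 | 21.8 |

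For f = 2%: 32 × 0.98 = 31.36 and 31.36 − 17 = 14.36; adding 2 gives 16.36. Relative to 15.0, imputation would overstate the difference by at most 0.6 points or understate it by at most 1.4.

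**4. Power.** With 170 evaluable patients per arm, power is 89.9% with no exits. With every exit a non-responder it is 88.7%, 87.5%, 83.1% and 73.7% for f = 1%, 2%, 5% and 10%.

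**5. Choice of f.** The article gives no exit rate. The 2% is the constipation rate that the section on 5HT3 receptor antagonist sensitivity reports under titration. It is only a proxy, because the exit requires hard stool to persist after two dose reductions. The 5% and 10% rows show when the issue would become material; the documents do not support them as expected rates.

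**The case against.** The strongest reply is that the sentence is loose shorthand in a paragraph about dosing and means stopping the capsules. The analysis sections point that way, since they keep all randomised patients and count treatment withdrawals separately. The article condenses a full protocol, and it refers to a standard operating procedure and a patient leaflet for titration; any of these may settle follow-up. This stands in part: the end of data collection is an inference from the wording. But what is printed is a rule, not a silence, and its literal meaning conflicts with the analysis principle.

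Several stronger readings are tempting and are not supported:

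- **That the intention-to-treat population is broken.** It is not. These patients remain in it and are imputed, and the sample size allows 15% attrition. The weakness is missing outcome data.
- **That the bias favours ondansetron.** The table runs both ways, because outcomes after stopping are unknown.
- **That the exits fall almost entirely on ondansetron.** More on active drug is plausible, but the rule is applied blinded to both arms. If placebo exits also ran at 2% with the same outcome, the difference would be 0.98 × 15 = 14.7 points.
- **That the effect could reach 8 points.** This would need the one-quarter constipation rate in Trial design to be the exit rate (0.25 × 32 = 8). That rate belongs to a standard dose, which titration is meant to avoid, and the article calls this exit unlikely.
- **That safety data in general are lost.** Anyone who takes one dose is in the safety set, serious events are reported to 28 days after the last dose, and withdrawals are tabulated with reasons. What could be missed is the checklist at visits 4 to 6.

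The planned sensitivity analyses help only in part. Complete-case analysis drops these patients, and pattern mixture modelling depends on a missingness pattern that about four patients are unlikely to reveal.

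**Conclusion.** The point holds as a conflict of wording with a modest consequence. Taken literally, the Dose titration rule ends follow-up for an exit linked to treatment effect. An early exit would then leave responder status almost wholly imputed under missing at random and lose the checklist at visits 4 to 6. At the assumed 2% exit rate the numerical effect is small and of uncertain sign, and only at about 5% to 10% would it matter to the result. The conclusion rests on the literal reading, on exits occurring mainly during titration, and on the constipation rate as a proxy for the exit rate. It is worth acting on because the loss is avoidable at almost no cost.

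**What to change.** Reconcile Dose titration with Endpoint analysis and Safety analyses so that this exit does not end data collection. State that a patient who meets the rule stops trial treatment but continues the diary, the text messages (if they agreed to them) and visits 4 to 6 unless they withdraw consent, and that the observed data enter the intention-to-treat analysis. Carry the same wording into the titration procedure for sites and the patient leaflet. The clinical rule for stopping treatment stays as it is.

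The cost is a minor wording change, an update to site instructions, and some continued contact with a few patients. The diaries, messages and visits already exist.

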### Outcomes

#### Primary outcome measure

The primary outcome measure is to ascertain whether 12 weeks of ondansetron increases the FDA-defined responder rate (in relation to abnormal defaecation and abdominal pain) compared with placebo. A responder is a patient who records both a reduction in pain intensity (≥ 30% decrease from baseline in weekly average worst daily pain) and improvement in stool consistency (≥ 50% decrease in the number of days per week with ≥ 1 loose stool ((BSFS) [21] 6 or 7)) for at least 6 weeks of the 12-week treatment period.

#### Secondary outcome measures

Secondary outcome measures will include:
Stool consistency and abdominal pain (measured by diary and daily text message);Stool frequency, urgency of defaecation, and use of rescue medication (defined as the use of loperamide) over 12 weeks of treatment and the answer to the question “Overall, have you had satisfactory relief from your IBS symptoms in the past week?” (measured by diary);The following will also be assessed at the beginning and the end of the trial: IBS symptom severity (measured by the Irritable Bowel Syndrome Severity Scoring System (IBS-SSS) [22]), dyspepsia (using the Short Form Leeds Dyspepsia Questionnaire (SF-LDQ) [23]), quality of life and mood (using the Irritable Bowel Syndrome Quality of Life (IBS-QOL) [24] and Hospital Anxiety and Depression Scale (HADS) [25] questionnaires), and somatic symptoms (using the Patient Health Questionnaire 12 Somatic Symptoms (PHQ-12) [26] questionnaire);Stool frequency, stool consistency, urgency, abdominal pain, and adverse events (AEs) assessed 4 weeks after the end of treatment to determine if there are any persisting effects.

